**Figure 2 fig2:**
[figure not shown]
Gantt chart of research activities. *: Lengths of outcome evaluations at each time point, intervention, and follow-up will be 1 month, 4 months, and 3 months, respectively. As participant recruitment will last 2 months, an additional month has been added to each activity. #: Time schedule of intervention delivery in this figure is appropriate for participants recruited in the 10th month only. Time schedule for those recruited in month 11 will be extended accordingly.

### Data analysis

2.9

All data analyses will be conducted using SPSS version 29. Descriptive statistics will be used to describe the baseline characteristics of participants. The primary analyses will use intention-to-treat analysis involving all randomised participants at baseline (77). Missing data from both dropouts and completers will be imputed using a multiple imputation (MI) approach with chained equations before the analysis (78). Further, generalised linear mixed models (GLMM) will be applied to evaluate the intervention effects on outcome measures at baseline, post-intervention, and follow-up, with time, groups, and their interaction as fixed effects. The baseline values showing significant differences across groups will be controlled as covariates, while elderly clusters and individuals will be treated as random effects. *Post-hoc* tests will be conducted if a significant interaction effect is detected using the sequential Sidak method for multiple comparisons. The intra-class correlation coefficient (ICC) will be calculated to identify the variance between elderly centres. The significance level will be set as 95% (two-tailed), and the effect size Cohen’s *d* will be calculated for within and between groups, where *d* = 0.30, 0.50, 0.80, indicating a small, medium, and large effect size, respectively.

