### Study design

2.1

This study will be a single-blinded three-group cluster-RCT to examine the effects of HIIT intervention on depression symptoms, physical fitness, sleep quality, and quality of life immediately after a 16-week intervention and the residual effects 3 months following completion of the intervention. A cluster random sampling method will be adopted to recruit the participants. With elderly centres used as a cluster unit for randomization and intervention, nine elderly centres in Hong Kong will be randomly assigned to three groups. Thus, participants will be randomly recruited and assigned through elder centres to one of three groups: a HIIT group, an exercise control group (Baduanjin Qigong), and a non-exercise control group (recreation workshops). Randomisation will be conducted using the random function available in Excel by a researcher who will not be involved in the participant recruitment and data collection. The block size for randomization will be 3, and the clusters within each block will be sorted by block number and a random number. Evaluation will be conducted at pre-intervention (T1), post-intervention (T2), and 3 months after intervention completion (T3). Outcome assessors will be blinded to the intervention assignment results. The CONSORT flow diagram (46) is presented in Figure 1.

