### Sample size estimation

2.3

According to government data, each neighbourhood elderly centre in Hong Kong must have at least 800 members per year (Social Welfare Department, https://www.swd.gov.hk/). All these conditions enable us to recruit sufficient older adults with mild and moderate levels of depressive symptoms to the centre. Hence, for a feasible study implementation principle, a cluster size of 16 was selected in the current study. An average medium effect size (Cohen’s *f* = 0.25 converted from *η*^2^ = 0.06) based on previous meta-analysis studies with HIIT interventions on depression (51), an alpha of 0.05, a statistical power of 90%, an ICC of 0.01, and a 30% attrition rate (43) are the parameters of the estimation. Sample size was calculated by G*Power 3.1.9.7 software, using repeated measures to detect the within-between interaction between ANOVA analyses of three assessments by three groups, and equation for cluster design = [1 + (n-1)*ρ*], *n* is the average cluster size, *ρ* is the intraclass correlation coefficient, which represents the correlation between observations within the same cluster (52). A total of 144 participants in 9 clusters (3 clusters with 48 participants each) will be required for this study.

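### The mixed model as described has no centre-by-time term, so the gating group-by-time test makes no allowance for centres that differ in change over time

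*Protocol article*

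**What the plan says.** Under Study design, the centre is the unit of randomisation and of intervention: "nine elderly centres in Hong Kong will be randomly assigned to three groups". That is three centres per arm, with 16 participants planned in each.

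Under Data analysis, a generalised linear mixed model is fitted to baseline, post-intervention and follow-up values "with time, groups, and their interaction as fixed effects", "while elderly clusters and individuals will be treated as random effects". The arm comparisons depend on the interaction: post-hoc "tests will be conducted if a significant interaction effect is detected using the sequential Sidak method for multiple comparisons". No random slope, centre-by-time term, link function or degrees-of-freedom method is named.

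Under Sample size estimation, the trial is sized on that same interaction, "using repeated measures to detect the within-between interaction between ANOVA analyses of three assessments by three groups". The inputs are "an alpha of 0.05, a statistical power of 90%, an ICC of 0.01, and a 30% attrition rate", Cohen's f of 0.25 and a design effect of 1 + (n − 1)ρ.

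**The concern.** Baseline is one of the modelled outcomes, so the treatment effect sits in the group-by-time interaction, which is a contrast of within-person changes. A constant added to everyone in a centre, or to one person at every visit, drops out of such a contrast. The centre effect in the model looks like protection against clustering but gives none to this test. What matters for the test is whether centres differ in how much they change, and no term in the description carries that.

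The two sections also disagree. The sample size section treats clustering as relevant to the interaction and pays 15% for it. The analysis section, on its plain reading, gives it no weight in that test. Ordinary differences between centres in change could then pass the gate and be reported as an exercise effect. The ICC that the plan will calculate for variance between centres would not clearly show this, because the missing component is variation in change, not in level.

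**Working it through.** **1. The plan's own figure.** Inputs from Sample size estimation: f = 0.25, alpha 0.05, power 90%, ICC 0.01, cluster size 16, attrition 30%. The correlation ρ between repeated measures is not given. For the within-between interaction with m = 3 assessments, the noncentrality is f²·N·m/(1 − ρ) on 4 and 2(N − 3) df.
- With ρ = 0: N = 85 gives 0.0625 × 85 × 3 = 15.9 and power 90%. Rounded to three equal arms, N = 87.
- Design effect: 1 + 15 × 0.01 = 1.15. Then 87 × 1.15 / 0.70 = 143, and 9 × 16 = 144. The figure is reproduced.
- It is not reproduced at other values: ρ = 0.25 gives 109 and ρ = 0.5 gives 74.

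**2. Cancellation.** Write y = fixed part + centre effect + person effect + residual. In any difference between two visits of one person, the centre and person effects subtract out. A numerical check agrees. Random-intercept models were fitted to one simulated data set (9 centres of 16, three visits) with the centre effect scaled over a 15-fold range. All four interaction estimates, their standard errors (0.2059) and the Wald statistic (3.81) stayed the same.

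**3. Size of the test when centres differ in change.** Let κ be the ICC of the time contrasts. With total variance 1, person correlation 0.5 (assumed) and centre correlation over time r (assumed), κ = ICC × (1 − r)/(1 − 0.5). The interaction mean square is inflated by D = 1 + (n − 1)κ. The within-person mean square is about W = [12D + (d − 12)(1 − κ)]/d, with d = 2(9n − 3). Type I error is about P(F(4, d) > c·W/D), where c is the 5% critical value.

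Example with n = 16, ICC 0.01 and r = 0.5:
- κ = 0.01 × 0.5/0.5 = 0.01; D = 1.15; d = 282; c = 2.404.
- W = (12 × 1.15 + 270 × 0.99)/282 = 0.997.
- c·W/D = 2.08, and P(F(4, 282) > 2.08) = 8.3%.

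At the plan's ICC of 0.01, with 20,000 simulated null trials per cell:

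| n per centre | r | κ | D | Formula | Simulated |
|---|---|---|---|---|---|
| 16 | 1 | 0 | 1.00 | 5.0% | 5.0% |
| 16 | 0.8 | 0.004 | 1.06 | 6.2% | 6.2% |
| 16 | 0.5 | 0.01 | 1.15 | 8.3% | 8.4% |
| 16 | 0 | 0.02 | 1.30 | 12.2% | 12.0% |
| 11 | 1 | 0 | 1.00 | 5.0% | 5.2% |
| 11 | 0.8 | 0.004 | 1.04 | 5.8% | 5.6% |
| 11 | 0.5 | 0.01 | 1.10 | 7.1% | 7.2% |
| 11 | 0 | 0.02 | 1.20 | 9.6% | 9.5% |

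Repeat simulations agreed to within about half a percentage point. The rows with 11 per centre reflect 16 × 0.70 = 11.2.

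**4. The test with a centre-level error term.** The error df are (9 − 3) × (3 − 1) = 12 for the omnibus interaction, and 9 − 3 = 6 for a pairwise change contrast that pools the centres of all three arms. The critical F for the omnibus test is 3.26 on 4 and 12 df, against 2.40 on 4 and 282. Simulated type I error of the centre-level omnibus test stayed at about 5% in every setting.

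**5. Power with 12 error df** (f = 0.25, κ = 0.01):
- All 144, ρ = 0: noncentrality 0.0625 × 144 × 3/1.15 = 23.5; power 91%.
- After 30% attrition, ρ = 0: D = 1 + 10.2 × 0.01 = 1.102; noncentrality 0.0625 × 100.8 × 3/1.102 = 17.2; power 79%.
- After attrition, ρ = 0.5: noncentrality 34.3; power 98%.

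**The case against.** The strongest reply is that the article says neither intercept nor only. Random-effects structure, link and denominator df are often left to a full protocol or analysis plan, and none is shown here. That stands as a caution: reading the terms as intercepts is an inference, although the plain one. It does not remove the point, because the article does state which units get random effects, and that statement does not match the clustering factor applied to the same test.

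Two technical limits also stand. Exact cancellation needs an identity link and balanced data, and the link for the GDS-15 score is not stated. Intercepts also do not cancel from between-arm comparisons of means at a single visit, and the article does not say which form the post-hoc tests take.

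A reader might infer three stronger things that the document does not support:
- **That the test certainly exceeds 5%.** It does so only if centre-by-time variance is above zero, and the document gives no value for that variance.
- **That having three centres per arm causes the excess.** The excess depends on centre size and κ. The number of centres fixes the error df once the term is included.
- **That rejection rates of 25% or 40% are to be expected.** Such rates need an ICC of about 0.05, five times the plan's and without a source here, together with a centre correlation over time of 0.5 or lower.

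**Conclusion.** The point holds in conditional form. As described, the gating test carries no allowance for centre differences in change, and this conflicts with the design effect used to size it. At the plan's own ICC the excess over 5% is roughly 1 to 7 percentage points with 16 per centre and 1 to 4.5 points with 11, for centre correlation over time between 0.8 and 0. It is zero if all centre differences are constant over time.

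These sizes rest on an assumed person correlation of 0.5, balanced data and an identity link. They fall if the person correlation is lower. At the value of 0 needed to reproduce 144, κ equals ICC × (1 − r), so with 16 per centre the rates are 6.6% for r = 0.5 and 8.3% for r = 0. A person correlation above 0.5 would raise them. Nothing in the document supports assuming zero variation in change between centres that are both the unit of randomisation and the unit of intervention. The matter should be settled before analysis.

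**What to change.** State the random-effects structure and link in full. Then do one of the following:
- Add a centre-by-time random effect, and test the interaction and the T2 and T3 arm contrasts with Satterthwaite or Kenward-Roger df.
- Analyse centre-level means, with 12 error df for the omnibus interaction and 6 for a pairwise change contrast.

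Restate the power for the chosen test, giving the assumed correlation between repeated measures.

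The change itself is one model term and one df option. The price is wider intervals and lower power: about 79% after 30% attrition if the repeated measures are uncorrelated, against the stated 90%, but 98% if their correlation is 0.5. The mixed-model version may also be mildly conservative. In a check at ICC 0.01 with 16 per centre, the centre-by-time variance was estimated as zero in about 31% to 49% of null trials, and the test rejected in about 3.4% to 4.6%. The centre-level version kept close to 5%.

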### Study participants

2.2

The target participants will be community-dwelling older adults with mild to moderate depressive symptoms in Hong Kong. The following selection criteria will be employed to screen for eligibility: (1) 60 to 74 years at the start date of the project; (2) Chinese version of Geriatric Depression Scale (GDS-15) scoring 5–11 (i.e., mild to moderate level of depressive symptoms) (47); (3) pass the PAR-Q + screening (48) or with the physician’s approval for readiness of participation in the high-intensity exercise; (4) no severe chronic diseases, such as coronary heart disease, chronic heart failure, chronic obstructive pulmonary disease, osteoarthritis, which are diagnosed clinically in the medical history; (5) reach the average level of 2-min step test (aerobic fitness; ≥ 94 counts for male and female), 30 s sit and stand (lower limb strength; ≥ 15 counts 94 for male and female), and the timed up and go fitness test (mobility and dynamic balance; ≤ 5.9 s for male and female) showing physical competence for high-intensity exercise, based on the fitness norm of Chinese community-dwelling older adults (49); (6) no cognitive impairment, as determined by the Chinese version of the Mini-Mental Status Examination (i.e., score ≥ 24) (50); (7) No previous substantial experience in practicing HIIT or Baduanjin Qigong. A signed written informed consent form will be collected from each participant.

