##### Depressive symptoms

2.6.1.1

The Chinese version of the 15-item Geriatric Depression Scale (GDS-C) will be used to measure depressive symptoms (47). The GDS is the most widely used scale for detecting depression symptoms in older adults (Cronbach’s *α* = 0.81–0.83). Participants will be asked 15 items, such as “Are you satisfied with your life in the past week?.” Answers are given on a yes/no scale. The total score ranges from 0 to 15, where 0–4 = normal, 5–8 = mild depressive symptoms, 9–11 = moderate depressive symptoms, and 12–15 = severe depressive symptoms (36).

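### Section 2.9 names only random effects for centres and individuals; read as random intercepts, this assumes equal variances and correlations across T1–T3 and may misstate the standard errors of the arm contrasts

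*Protocol article*

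**What the plan says.** Section 2.9 (Data analysis) plans generalised linear mixed models for the outcomes at all three assessments, "with time, groups, and their interaction as fixed effects", so baseline is one of the modelled outcome times. Dependence is addressed in one clause: "while elderly clusters and individuals will be treated as random effects". The article mentions no random slope, repeated effect, residual covariance structure or robust standard error, and excludes none. It names no distribution or link.

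Arm contrasts are conditional: post-hoc "tests will be conducted if a significant interaction effect is detected using the sequential Sidak method for multiple comparisons". The test level is two-sided 0.05, although section 2.9 words it as "The significance level will be set as 95% (two-tailed".

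Three features of the design bear on the covariance:

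- Section 2.2 requires for entry a "Chinese version of Geriatric Depression Scale (GDS-15) scoring 5–11", whereas section 2.6.1.1 says of the same scale, as primary outcome, "The total score ranges from 0 to 15".
- Section 2.8 places T1 within one month before the programme, in people already found eligible.
- The footnote to Figure 2 gives a 4-month intervention and a 3-month follow-up.

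**The concern.** One intercept per centre and one per person give every visit the same variance and every pair of visits the same covariance (compound symmetry). The variance of a within-person change is then the same for T1 to T2, T1 to T3 and T2 to T3.

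The design gives reasons to doubt this. T2 and T3 lie on the same side of the intervention and about 3 months apart, so they may well correlate more strongly with each other than either does with T1. Correlation may also simply decay with time. Individuals may respond differently to the programmes, which adds variance at T2 and T3 but not at T1. Selection on GDS 5–11 may compress the spread at T1.

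Both hypotheses in the Introduction rest on arm contrasts at T2 and T3. If the covariance is wrong, their p-values and confidence intervals are too optimistic at one visit and too wide at another. This is a person-level matter. It would remain even if all centres responded identically.

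**Working it through.** **The plan's own figures.** On this point the article states only the design inputs "an alpha of 0.05, a statistical power of 90%, an ICC of 0.01, and a 30% attrition rate" and the total of 144. That total can be reproduced. For the 3 × 3 within-between interaction with f = 0.25, between-visit correlation 0 and no nonsphericity correction, 90% power needs 85 people, or 87 in equal arms. Then 87 × 1.15 = 100.05, and 100.05 / 0.70 = 142.9, so 143, or 144 in whole clusters of 16. With correlation 0.5 the same chain gives about 74. The calculation therefore does not reveal what SDs or correlations are expected for GDS.

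**Inputs for the check.** From the article: 48 per arm, three visits, two-sided 0.05. Assumed, because the article gives none: all SDs and correlations. Simplifications: Gaussian outcome, complete data, no centre effect.

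**Formula.** For visits j and k, the true variance of the change is V = s_j² + s_k² − 2·r·s_j·s_k. With complete data, the random-intercept model uses the mean D of the three V values for every change contrast. The ratio of model to true standard error is √(D/V). With (144 − 3) × 2 = 282 degrees of freedom, the true type I error is 2·[1 − T₂₈₂(1.968·√(D/V))].

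**Worked example (case A).** SDs 3/3/3; correlations 0.5 (T1–T2), 0.5 (T1–T3), 0.7 (T2–T3).

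- V = 9 + 9 − 2·0.5·9 = 9 for T1–T2 and for T1–T3.
- V = 18 − 2·0.7·9 = 5.4 for T2–T3.
- D = (9 + 9 + 5.4)/3 = 7.8, and √(7.8/9) = 0.931.
- Standard error of an arm difference in change: model √(2·7.8/48) = 0.570, true √(2·9/48) = 0.612. The model is 7% too small, and type I error is 6.8%.

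| Case | SDs | Correlations | V (T2−T1; T3−T1; T3−T2) | D | Type I, T2 / T3 change |
|---|---|---|---|---|---|
| Control | 3/3/3 | 0.5/0.5/0.5 | 9; 9; 9 | 9 | 5.0% / 5.0% |
| A | 3/3/3 | 0.5/0.5/0.7 | 9; 9; 5.4 | 7.8 | 6.8% / 6.8% |
| B | 2/3/3 | 0.4/0.4/0.7 | 8.2; 8.2; 5.4 | 7.27 | 6.5% / 6.5% |
| C | 2/3/3 | 0.3/0.3/0.8 | 9.4; 9.4; 3.6 | 7.47 | 8.0% / 8.0% |
| D | 3/3/3 | 0.6/0.36/0.6 | 7.2; 11.52; 7.2 | 8.64 | 3.2% / 8.9% |
| E | 2/3/3 | 0.4/0.4/0.6 | 8.2; 8.2; 7.2 | 7.87 | 5.5% / 5.5% |

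Simulation (20,000 trials per case) agreed: 7.0% for A, about 7% for B, 8.0% for C, 3.2% and 9.3% for D, 5.4% for E, and 4.9–5.3% for the control. The T1 SD of 2 is that of a uniform spread over GDS 5–11.

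**Direct comparison of arms at T2 or T3.** Here the model uses the total variance averaged over visits. With SDs 2/3/3 that is (4 + 9 + 9)/3 = 7.33, SD 2.71. The ratio is 2.71/3 = 0.903, so the standard error is 10% too small. Type I error is 2·[1 − Φ(1.96 × 0.903)] = 7.7%.

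**The planned gate.** Under the global null, over assumed scenarios of this kind, the interaction test itself runs at 5.1–6.4%, and change contrasts that must first pass it at 1.1–3.4% before Sidak. If one arm truly differs, the gate opens. With HIIT 3 points better (chosen large so that it always opens), Baduanjin equal to workshop, sequential Sidak within each visit and 8,000 trials, the false-positive rate for Baduanjin versus workshop (change to T2 / T3) is:

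- control: 4.4% / 4.9%
- A: 6.5% / 6.9%
- B: 6.7% / 7.0%
- C: 8.0% / 7.6%
- D: 3.0% / 8.6%

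The simulation error near 5% is about √(0.05 × 0.95/8,000) = 0.24 percentage points.

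**The case against.** The strongest reply is that the article never says random intercept only. It neither states nor excludes a residual covariance, random slopes or robust standard errors, and such detail often sits in a statistical analysis plan. With a non-identity link, equal variances would not follow. This stands against any claim that the text forces compound symmetry. It does not remove the point, because the article does name one device for within-person dependence, and the ordinary reading of it is an intercept.

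A reader might infer that the standard errors are simply wrong and that the error rate is 3–9%. The documents do not support that. Every SD and correlation is assumed, and case E is close to nominal. Both ends of the range come from case D, which has equal SDs and equally spaced decay. Re-spacing that decay to the article's 4 and 3 months gives 4.1% at T2 and 9.0% at T3. Nor is 3–9% a bound: over a wider grid of assumed values (T1 SD 1.5–2.0, later SDs 2.0–3.5, correlations 0.2–0.8), the middle 90% of results was 0.5–8.6% for T2 and 3.2–12.7% for T3.

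A reader might also blame the entry restriction for the distortion of the change contrasts. In these cases it works the other way. With correlations fixed at 0.5/0.5/0.7, lowering the T1 SD from 3 to 2 moves the error from 6.8% to 6.0%; at 0.3/0.3/0.8, from 8.7% to 8.0%. A smaller T1 variance matters mainly for direct arm comparisons at T2 or T3. It is also weaker if GDS is re-measured at T1 after screening, which section 2.8 leaves possible, and improvement towards the floor of 0 could compress the later visits. The argument from GDS selection does not carry over to cortisol, sleep or quality of life.

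The gate and the Sidak step do limit the error under the global null. They do not protect the remaining comparison once one arm truly differs, and they do nothing for the width of confidence intervals.

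**Conclusion.** The point holds in a conditional form. On the ordinary reading of section 2.9, the model assumes equal variances and equal correlations across T1–T3, which visit order and timing make doubtful. If that fails, standard errors of the arm contrasts are too small or too large depending on the visit.

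Under the assumed values, a single change contrast has a type I error between about 3% and 9%, with some plausible cases near 5%. A direct comparison at T2 or T3 would be at about 7.7% with SDs 2/3/3. These figures rest on a Gaussian outcome, complete data and no centre effect, whereas the plan has 30% attrition, multiple imputation and centre random effects. This is a cheap improvement to the primary model. It is not a demonstrated error in a stated result.

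**What to change.** In section 2.9, for the continuous outcomes, replace the individual random intercept with an unstructured 3 × 3 within-person residual covariance over T1, T2 and T3 (visit as a repeated effect). Keep the centre random effects. Name this as the primary structure, and the random-intercept model as a fallback only if it does not converge.

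The cost is one sentence and no extra data. The person-level part then has six covariance parameters instead of two, estimated from 144 people, with some risk of non-convergence that the stated fallback covers.
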